## Measures

### Primary outcome

Post-discharge home days at 90 days: Home days will be calculated as days alive and at home, a composite of mortality and morbidity. We included mortality to ensure that competing risk of death will not affect this outcome. The proposed interventions are likely to have a small effect on time to death in these patients.

### Secondary outcomes

Functional Status: will be measured at baseline and 90 days, using the PROMIS Physical Function – for Mobility Aid Users-SF. The Patient-Reported Outcomes Measurement Information System (PROMIS™) provides item banks that offer the potential for PRO measurement that is efficient (minimizes item number without compromising reliability) flexible (enables optional use of interchangeable items), and precise (has minimal error in estimate) measurement of commonly-studied PROs. PROMIS item banks and their short forms provide evidence they are reliable and precise measures of generic symptoms and functional reports comparable to legacy instruments.

Health-related Quality of Life: will be measured at baseline and 90 days, using the Quality of Life Enjoyment and Satisfaction Questionnaire-SF. The Quality of Life Enjoyment and Satisfaction Questionnaire (Q-LES-Q) is a self-report measure designed to enable investigators to easily obtain sensitive measures of the degree of enjoyment and satisfaction experienced by subjects in various areas of daily functioning.

Transition to Hospice: will be assessed via claims data at 90 days to see if member transitioned to hospice care during the course of the study.

Emergent outpatient utilization: will be assessed via claims data at 90 days for a count of urgent outpatient visits for study participants.

Readmissions: will be assessed via claims data at day 7, 30, and 90 for any inpatient admissions after index admission, and whether readmission hospital was the same as index hospital.

Mortality: will be assessed via claims data at 90 days to see if and when the member/participant passes away.

### Covariates

We will include variables likely to influence the strength of the relationship between the interventions and outcomes and included variables within domains (patient-level, socioecological, and care delivery and utilization) that have hypothesized associations with the primary and secondary outcomes. These covariates will be the basis for Aim 2 analyses. Finally, we will monitor adherence to pre-established intervention workflows and RPM response rates throughout the study to ensure that intervention fidelity is maintained and can be accounted for in the analyses.

### Domain: Patient-Level:

Patient Demographics and clinical characteristics: We include in our baseline survey questions regarding age, race, ethnicity, marital status, and gender. Insurance type and the Charleston Comorbidity index will be pulled from administrative and claims data at baseline. We will ask questions about generalized anxiety disorder, depressed mood and anhedonia, health literacy, and comfort with technology.

Living at home status: We include in our baseline and 90-day survey questions regarding whether a participant lives at home alone or with others. If participants live with others, an additional question to identify their living companion(s) is asked. The participant can identify multiple living companions from a list.

Payer: Based on literature review and the experience of our study investigators, we do not expect large differences in the distributions of post-discharge home days between UPMC Health Plan and MC FFS study participants. However, in the event that participant payer (UPMC Health Plan or MC FFS) is predictive of home day distribution, randomization of study interventions ensures that effectiveness comparisons are guaranteed to remain unbiased toward any particular arm. Thus, our primary analysis model will remain as it is currently stated in the Statistical Analysis Plan.

To maximize oversight the proposed new subgroup (MC FFS), home days distributions of each payer type group will be reported to the DSMB in regular quarterly interim analysis reports. In addition, we will conduct two types of sensitivity analyses to detect any differences in the two distributions after data collection:

1. We will fit two additional proportional logit models accounting for payer type:
  - a. One logit model including a term for payer which will capture proportional shifts in home days across payer groups; and
  - b. A second model that will include different intercept terms for the payer type groups. This model will capture non-proportional shifts in home days across both groups.
2. We will explore potential differential effects of RPM care models across payer types. One model will estimate interaction terms between RPM arm and payer type; and another will fit separate proportional logit models to UPMC Health Plan and MC FFS participants.

Domain: Socioecological:

Distance to primary care provider (PCP) office: Distance from participant's home address to the PCP office in miles will be pulled from administrative data at baseline.

Area Deprivation Index (ADI): The ADI will be a composite score of socioeconomic variables to indicate neighborhood socioeconomic status pulled from administrative data at baseline.

Domain: Care Delivery and Utilization:

Non-urgent outpatient care utilization: The count of non-urgent outpatient visits that occur per participant during the observation period (primary and specialty care visits) will be pulled from claims data at 90 days.

Prior admissions: The number of inpatient admissions in 90 days prior to index admission will be pulled at baseline from claims data.

ICU stay, mechanical ventilation, inpatient dialysis: Whether participant received each type of care during index hospitalization and if so, for how many days will be pulled at baseline from the electronic health record and claims data.

Skilled nursing facility stay: Whether a patient had a post-index hospitalization stay in a SNF for 28 days or fewer before being discharged home.

Index hospital: The location of the index hospitalization, hospital bed size, and hospital teaching status will be pulled from claims data at baseline.

540 A summary of measures is shown below:

| STUDY VARIABLES                                      | DATA SOURCE                                                                | WHEN MEASURED      | HOW MEASURED                                                                                                                         |
|------------------------------------------------------|----------------------------------------------------------------------------|--------------------|--------------------------------------------------------------------------------------------------------------------------------------|
| Primary Outcome                               |                                                                            |                    |                                                                                                                                      |
| Post-discharge home days                             | Claims data, EHR data, Health Information Exchange (HIE) data, Participant | 90 days            | Total number of days alive and out of acute care hospitals, inpatient rehabilitation, or skilled nursing facilities  |
| Secondary Outcomes                            |                                                                            |                    |                                                                                                                                      |
| Functional status                                    | Participant                                                                | Baseline, 90 days  | PROMIS Physical Function – for Mobility Aid Users                                                                    |
| Health-related Quality of Life                       | Participant                                                                | Baseline, 90 days  | Quality of Life Enjoyment and Satisfaction Questionnaire-SF (QLESQ-SF)                                                  |
| Transition to Hospice                                | Claims data                                                                | 90 days            | Whether member transitioned to hospice care                                                                                          |
| Emergent outpatient utilization                      | Claims data, EHR data, HIE data, Participant                               | 90 days            | Count of urgent outpatient visits (ED visits & urgent care visits)                                                                   |
| Readmissions                                         | Claims data, EHR data, HIE data, Participant                               | 7, 30, and 90 days | Subsequent inpatient admission after index admission, and whether readmission hospital was same as index hospital       |
| Mortality                                            | Claims data, EHR data                                                      | 90 days            | Whether member dies during observation period                                                                                        |
| Covariates                                    |                                                                            |                    |                                                                                                                                      |
| Domain: Patient-Level                         |                                                                            |                    |                                                                                                                                      |
| Patient demographics & clinical characteristics      | Administrative & claims data                                               | Baseline           | Age, race, gender, insurance type, Charlson Comorbidity Index                                                        |
| Living at home status                                | Participant                                                                | Baseline           | Whether participant lives alone or with others                                                                                       |
| Payer                                                | EHR data                                                                   | Baseline           | Whether participant is insured by UPMC Health Plan or Medicare Fee-for-Service                                                       |
| Domain: Socioecological                       |                                                                            |                    |                                                                                                                                      |
| Distance to primary care provider (PCP) office       | Administrative data                                                        | Baseline           | Distance from participant's home address to PCP office (miles)                                                                       |
| Area Deprivation Index (ADI)                         | Administrative data                                                        | Baseline           | Composite score of socioeconomic variables to indicate neighborhood SES                                                 |
| Domain: Care Delivery & Utilization       |                                                                            |                    |                                                                                                                                      |
| Non-urgent outpatient care utilization               | Claims data, EHR data, Participant                                         | 90 days            | Count of non-urgent outpatient visits that occur during the observation period (primary and specialty care visits)                   |
| Prior admissions                                     | Claims data, EHR data                                                      | Baseline           | Number of inpatient admissions in 90 days prior to index admission                                                                   |
| ICU stay, mechanical ventilation, inpatient dialysis | EHR/Claims data                                                            | Baseline           | Whether participant received each type of care during index hospitalization and if so, for how many days                             |
| Skilled nursing facility stay                        | EHR/clinicians                                                             | Baseline           | Whether the patient had a post-index hospitalization stay in a SNF for 28 days or fewer before being                                 |

|                            |                            |          |                                                                           |
|----------------------------|----------------------------|----------|---------------------------------------------------------------------------|
|                            |                            |          | discharged home                                                           |
| Index hospital             | EHR/Claims data            | Baseline | Location of index hospitalization, hospital bed size, and teaching status |
| Process             |                            |          |                                                                           |
| Integrity of care/fidelity | Research staff, clinicians | 90 days  | Checklist for RM and care approaches/processes                            |
| RPM compliance             | Research staff, clinicians | 90 days  | RPM response rates                                                        |

## Process measures

The study team will monitor adherence to pre-established intervention workflows and RPM response rates throughout the study to ensure that intervention fidelity is maintained and can be accounted for in the analyses.

**Integrity of care/fidelity:** The research staff in conjunction with the remote monitoring supervisors following the RPM usual workflow, have developed an Interrater Reliability checklist to monitor fidelity to RPM intervention protocols and processes. This check will be conducted by either supervisors or peers every quarter to ensure established processes are being followed.

Fidelity to the STS arm protocol will be ensured by the telephonic case manager supervisor's routine monitoring of post-discharge phone calls. The research team will receive quarterly reports documenting that each study participant randomized to the STS arm received the STS usual care activities in accordance with usual care.

**Participant RPM compliance:** The research staff will review RPM response rate data at 90 days to characterize patient compliance to the RPM interventions.

**No Response:** Participants who are enrolled in the RPM program, but do not begin the RPM program on their electronic device will be contacted by the RPM call center staff to address any technology issues or questions that have arisen during the first seven days of enrollment. If the patient still has not interacted with the RPM program after 14 days, the Research Team will attempt one final call to the participant to address issues. If the participant still does not participate after the call from the Research Team, the participant will remain able to join the program at any point during the 90-day post-discharge intervention period, but will no longer be contacted and encouraged to participate in the program by the research team or the RPM staff.

**Non-Responder:** Patients who start the RPM program but fail to respond to RPM questions for 2 consecutive weeks are considered "non-responders". The remote monitoring call center staff will review non-responders' charts for hospital readmission, death, or admission to hospice. If the patient has not been readmitted, died, or went to hospice, they will be contacted by RPM staff to offer assistance and encouragement to respond. If there is still no participation after RPM staff outreach, the participant will continue to receive automated invitations to respond to pathways, but will no longer be encouraged to participate by the research team or RPM staff.

## Study Duration/ Timeline

*August 1, 2020 – December 31, 2020: Pre-Implementation Period*  
*January 1, 2021 – October 31, 2024: Implementation Period*  
*November 1, 2024 – July 31, 2026: Post-Implementation Period*

Participants will be consented and enrolled in the hospital. Baseline surveys will be collected during participants' the first two weeks at home. The study observation period will be for 90 days post discharge to home (whether from hospital or SNF). Ninety-day surveys will be collected one week prior to and two weeks after the end of the observation period. This timeline is documented in the diagram below.

[figure not shown]

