## Randomization Procedure

The study will use web-based randomization to one of the five care models for those individuals who consent to participate in the study. Once a research coordinator determines eligibility, obtains informed consent, and the patient is discharged to home while maintaining eligibility, he or she will enter in key identification information, and the system will then generate a Study ID (numeric identification number) along with assignment to an intervention arm. Randomization will initially be fixed with 30% of patients randomized to STS and the remaining 70% of patients randomized 1:1:1:1 between the four RPM care models. After 250 patients have been randomized and followed for 90 days, the first interim analyses will be conducted and RAR will begin and continue to be updated every three months. During the RAR phase, the randomization to STS will remain fixed to be 30% of patients and the remaining 70% of patients will be randomized to one of the four RPM models preferentially based on the probability that each RPM care model is optimal.

While the research coordinators will see each assigned intervention arm per the randomization process, they will be blinded to overall changes in treatment allocation rates. Other study team members, including Principal Investigators, Co-Investigators, statistical analysts, and database administrators will also be blinded to treatment allocation rates during the course of data collection.

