5.1. Timing initiation of interventions

Participants will be enrolled in the

appropriate intervention (as randomized) by their first full week day home from the hospital or skilled nursing facility (SNF). Participants enrolled in a RPM arm will be contacted by a research coordinator by telephone and encouraged to download the RPM application and initiate the program. If enrolled in structured telephone support, they will receive a post-discharge phone call per usual care timing.

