#### 8.10.2. Analysis of effect heterogeneity across pre-determined subgroups

We will conduct differential treatment effects analyses, comparing differences between RPM groups and STS across pre-specified subgroups of patient-level clinical, social, and environmental factors that could be potentially used to tailor service delivery. All analyses will be performed using a cumulative logit model for the primary PDHD outcome, including terms for treatment arm, subgroup, treatment by subgroup interactions, stratification variables, and calendar time of randomization. Subgroup variables and definitions were determined as plausibly related to treatment effect heterogeneity. Each subgroup variable will be analyzed in two ways: 1) four RPM arms kept separate; and 2) comparing standard team and enhanced team arms. Analyses will not be adjusted for multiple comparisons. Evidence of differential treatment effects across subgroup levels will be summarized using the posterior probability that interaction

terms are greater than 0. In addition, treatment effects by subgroup level will be summarized using the posterior median cumulative odds ratios from each model, and corresponding 95% credible intervals.

Subgroup definitions are as follows:

- Patient Age
  - <65 vs age ≥65
- Sex
  - Female vs male
- Race
  - White patients vs Black patients
- Chronic Condition index
  - CCI<5 vs CCI≥5
- Level of comfort with technology
  - Comfortable vs uncomfortable vs missing
- Health literacy level
  - Limited vs marginal vs adequate vs missing
- State-ranked Area Deprivation Index
  - Quartile 1 vs quartile 2 vs quartile 3 vs quartile 4 vs missing
- Location after discharge
  - Skilled Nursing Facility vs home
- Severity of illness
  - Severe (mechanical ventilation or vasopressor use during index hospitalization) vs not severe
- Discharge diagnosis
  - COVID vs Non-COVID Sepsis vs Other lower respiratory tract infection

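### Comfort with technology and health literacy are treated as baseline subgroups for Aim 2 but are measured after randomization, and their missing level is formed after randomization too

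*Combined protocol and SAP*

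**What the plan says.** The protocol's Randomization Procedure places assignment after consent and once "the patient is discharged to home while maintaining eligibility". SAP 5.1 has participants enrolled in the "appropriate intervention (as randomized) by their first full week day home from the hospital or skilled nursing facility (SNF"). In that section, participants in an RPM arm are "contacted by a research coordinator by telephone and encouraged to download the RPM application and initiate the program", whereas STS patients receive a post-discharge call on the usual-care schedule. Under Process measures, the call center contacts RPM participants who have not started, to "address any technology issues or questions that have arisen during the first seven days of enrollment".

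The protocol's Study Duration/ Timeline section says: "Baseline surveys will be collected during participants' the first two weeks at home". Its patient-level covariate paragraph describes the baseline survey and then says participants will be asked about health literacy and comfort with technology. Data Collection gives only two self-report occasions, baseline and 90 days.

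SAP 8.10.1 lists both variables among the baseline covariates for heterogeneity of treatment effect. SAP 8.10.2 uses both as subgroups. Comfort with technology is split as "Comfortable vs uncomfortable vs missing", and health literacy likewise has a missing category. Interactions are to be summarized by posterior probabilities, with no exception for the missing level.

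**The concern.** A subgroup analysis asks whether the effect differs between kinds of patient who were distinguishable before assignment. Two features of the plan weaken that reading here.

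First, the RPM arms include help with installing and using an app, and STS does not. If that help changes how patients rate their comfort with technology, the comfortable group in an RPM arm and the comfortable group in STS are no longer the same kind of patient. The mechanism is much weaker for health literacy.

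Second, a patient who dies or is readmitted soon after going home may not complete the survey, and both events lower post-discharge home days (PDHD). The missing level of both variables can therefore depend on early outcome. If completion also depends on arm, the effect within that level is distorted. In addition, the missing level does not exist at discharge, so it cannot help decide whom to offer RPM.

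What is at stake is the Aim 2 conclusion about who benefits. The protocol makes these covariates the basis for that aim, and the 8.10.1 list also feeds the multivariable effect models in 8.10.3.

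**Working it through.** **Step 1. Order of events (SAP Definitions: day 0 is the day of discharge home).**

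- Day 0: randomization (protocol, Randomization Procedure).
- By the first full weekday home: intervention enrollment, with the coordinator call in RPM arms only (SAP 5.1).
- First seven days: technology issues among RPM non-starters are followed up (protocol, Process measures).
- Days 0 to about 14: baseline survey (protocol, Study Duration/ Timeline).

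The gap from randomization to survey is thus 0 to about 14 days. SAP Definitions describes the study hospital as the place of randomization. If that wording governed, a skilled nursing stay of up to 28 days would extend the gap to 28 + 14 = 42 days. The survey follows randomization on either reading. The delayed reveal of allocation in the domain summary does not change this, because the arm must be known for the onboarding call. No section requires the survey before assignment or before that call.

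The plan gives no figure for the size of either problem, so there is nothing to reproduce. The illustrations below assume **no true effect in any patient** and use P(PDHD = 90) = 0.454 (SAP Appendix, Table 2). All other inputs are assumptions.

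**Step 2. Comfort changed by onboarding.** Assume 60% are truly comfortable, and that P(PDHD = 90) is higher by *d* in them. Then p0 = 0.454 − 0.6*d* (uncomfortable) and p1 = p0 + *d* (comfortable). In RPM arms a share *s* of uncomfortable patients reports being comfortable. Among those reporting comfort in RPM:

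P = (0.6·p1 + 0.4·*s*·p0) / (0.6 + 0.4·*s*)

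- *d* = 0.05, *s* = 0.10: p0 = 0.424, p1 = 0.474, P = 0.30136/0.64 = 0.471. OR against STS = 0.99.
- *d* = 0.15, *s* = 0.30: p0 = 0.364, p1 = 0.514, P = 0.35208/0.72 = 0.489. OR against STS = 0.91 (0.905).

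The OR in the uncomfortable level stays at 1.00. The distortion is modest over this range.

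**Step 3. Missing level.** Let *g* be the probability of a missing survey when PDHD = 90 (same in both arms), and m_S and m_R the probabilities when PDHD < 90 in STS and RPM. With q = 0.454, the odds of PDHD = 90 among missing patients are q*g* / [(1 − q)*m*]. Both q and *g* cancel in the arm comparison:

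- OR in the missing level = m_S / m_R
- OR in the observed levels = (1 − m_S) / (1 − m_R)

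| m_S | m_R | OR, missing | OR, observed | Ratio |
|---|---|---|---|---|
| 0.20 | 0.15 | 1.33 | 0.94 | 1.42 |
| 0.30 | 0.20 | 1.50 | 0.88 | 1.71 |
| 0.30 | 0.15 | 2.00 | 0.82 | 2.43 |
| 0.30 | 0.30 | 1.00 | 1.00 | 1.00 |

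The last row is the important limit. Dependence on outcome alone creates nothing under the null; completion must also differ by arm given outcome.

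**Step 4. How many patients.** At 1,281 enrolled with 30% to STS, there are about 384 STS and 897 active patients. A missing rate of 5–30% (assumed) would put about 19–115 STS and 45–269 active patients in the missing level.

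**Step 5. Two rules for the same gap.** SAP 8.11.2 plans ten imputed datasets for baseline covariates with missing data in secondary and sensitivity analyses, and 8.10.3 also mentions imputation models. SAP 8.10.2 keeps missing as a category. The plan does not say which applies to these two variables.

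**The case against.** The best case against the point is that it touches two of ten subgroup variables, in exploratory analyses without multiplicity adjustment, and that every distortion above rests on assumed rates. Most of that is right, and it limits the point in these ways.

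- **Order.** A reader might infer that every RPM patient is surveyed after onboarding. The documents do not fix the order for each patient: a survey on day 0 or 1 could come first, and the timeline diagram is not available here. What stands is that the plan permits the later order over most of the window.
- **Source of the items.** The measures table does not list comfort with technology or health literacy. That they come from the baseline survey is read from the covariate paragraph. The only other self-report occasion, day 90, is also after randomization.
- **Missingness.** A reader might infer that an outcome-related missing level is enough to invalidate the interaction. Step 3 shows that it is not. Differential completion is plausible because RPM arms have extra contacts, but it is not documented. Nor can a missing rate be read from the 23% 30-day readmission figure in the Background: readmitted patients may answer before or after the stay.
- **Comparisons among RPM arms.** Onboarding is common to all four, so these contrasts are less exposed to Step 2.
- **Late remedy.** The protocol ends implementation on October 31, 2024, and the SAP reference list includes a January 2025 publication. Moving the questions earlier may no longer be possible. The analysis changes still are.

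**Conclusion.** The point holds for Aim 2 in a limited form. Both variables are measured after randomization and, for most of the permitted window, after an RPM-only contact, yet the SAP calls them baseline. For comfort with technology, the plausible distortion is modest: OR 0.91–0.99 where 1.00 is true, assuming 10–30% of uncomfortable patients switch and a 5–15 point prognostic difference. For health literacy this route is weak. For both, the missing level is formed after randomization. It gives a spurious interaction under the null only if completion differs by arm given outcome; the ratio of 1.4–2.4 depends entirely on the assumed rates of 20–30% against 15–20%.

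A reader might infer that the primary result is compromised. The documents do not support that: the primary model adjusts for illness severity, skilled nursing discharge and calendar time, and uses neither variable. The Area Deprivation Index also has a missing level, but it comes from administrative data and does not share the timing problem.

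**What to change.** In SAP 8.10.1 and 8.10.2:

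1. Label comfort with technology and health literacy as measured after randomization, and interpret the comfort interaction accordingly.
2. Report by arm the survey completion rate and the survey date relative to randomization and to first RPM contact.
3. Show the missing level descriptively; do not report or interpret its interaction probability.
4. State whether the missing category or the imputation rule in 8.11.2 applies to these variables.
5. Add, as a sensitivity analysis only, results limited to surveys completed before first RPM contact, with a matched elapsed-time cut in STS. Say that this is itself a selection made after randomization and may leave few RPM patients.

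If any enrollment remains, ask these two sets of items at the in-hospital consent contact, before assignment; the function and quality-of-life questionnaires can stay where they are. Answers may be less reliable from patients with an altered mental state who enter by proxy consent.

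The analysis changes need no new patient contact. Their cost is a less precise exploratory subgroup result.
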